## 11.2 Secondary outcomes

1. 3 year PFS : PFS will be defined time in days between date of randomization to date of progression or death whichever is earlier. Patients who have not progressed or died at their last follow ups would be censored.The 3 year PFS would be estimated by Kaplan meier analysis and would be compared between the 2 arms by the log rank test. Cox proportional hazard model would be constructed for calculation of hazard ratio. The model would also be used to see the impact of chemotherapy regimen on 3 year progression survival in accordance with known prognostic factors. Age ( below or above 70 years), subsite , T stage, N stage, hemoglobin level ( equal to or below 10 g/dl or above it), and PS ( 0-1 versus 2).This information would be depicted in the form of a forest plot.
2. Toxicity : To compare CTCAE version 4.03 worst grade toxicity between the 2 arms during any period of chemotherapy. Chi- square test or fisher's test would be used for comparison. The NCI Common Terminology Criteria for Adverse Events version 4 (NCI CTCAE v4.03) will be used to classify and grade the intensity of adverse events after each treatment cycle. CTCAE will be used to collect all events regardless of attribution, in order to ensure objective reporting, and in order to report trial data according to accepted international guidelines. The worst toxicity would be recorded. The results would be computed in a tabular form in which the proportion of people having their highest grade of toxicity would be charted.
3. TOI ( Trial outcome index) : TOI will be calculated at baseline and at 6, 12,18,24 & 36months in both arms from FACT Head and neck QOL proformas. Increment in TOI of 6 units would be considered significant. Proportion of patients with significant improvement in TOI will be compared between 2 arms. Proportion test would be used for comparison.

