### 6.2.2 Secondary objectives

1. To compare the 3 year progression free survival of adjuvant metronomic chemotherapy with that of observation in patients with locally advanced head and neck cancers post radical chemoradiation . The secondary endpoint would be 3 year progression free survival.
2. To compare the grade 3-4 toxicity between adjuvant metronomic chemotherapy and observation
3. To compare the 6,12,18,24 & 36 months QOL scores between the 2 arms

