## 10.2 Arm A

In arm A **observation** would be done. The schedule of observation will be in accordance with the institutional follow up protocol which is as below

**First year** : Patient would be followed up at 3 monthly intervals. Clinical history and examination would be done. Blood investigations like complete hemogram, renal function tests and TSH would be done. FACIT QOL H&N would be filled at baseline,6 and at 12 months. The blood of patients of 10 ml would be collected at baseline, first follow up and at progression in both arms for future research purpose

**Second year** : Patient would be followed up at 3 monthly intervals. Clinical history and examination would be done. Blood investigations like complete hemogram, renal function tests and TSH would be done sos. FACIT QOL H&N would be filled at 18 & 24 months

**Third year-Fifth year** : Patient would be followed up at 6 monthly intervals. Clinical history and examination would be done. Blood investigations like complete hemogram, renal function tests and TSH would be done sos.

**Post fifth year** : Patient would be followed up at 1 year intervals. Clinical history and examination would be done. Blood investigations like complete hemogram, renal function tests and TSH would be done SOS.

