### 10.3.1 Schedule

Metronomic chemotherapy is the study intervention in this trial. The metronomic chemotherapy constitutes of methotrexate and celecoxib.

Oral methotrexate tablet 15 mg/m2 will be self administered weekly ie on D1,D8, D15 and D22 of every 28 day cycle.

Capsule celecoxib would will be self administered twice daily in a dose of 200 mg BID continuously .

The combination will be continued to a maximum of such 18 cycles; unless prohibitive toxicity or disease progression occurs prior to it. The schedule of visits of these patients would be similar to that in observation arm. Except that ECG and LFT would be done at each visit.

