**Table 3 : Timeline for participants in Arm : A**

***- CECT neck + scan of the relevant part would be done in accordance with the institutional standards.**

**#-Investigations will be done as per institutional standards and sos**

****- FACT H&N QOL would be collected at 6, 12,18,24 & 36 months from start of chemotherapy**

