**AEs are not required to be reported unless they meet SAE criteria.**

A SERIOUS ADVERSE EVENT (SAE) is any untoward medical occurrence that at any dose:

1. results in death,
2. is life-threatening (i.e. the subject is at risk of death at the time of the event),
3. requires inpatient hospitalisation or prolongation of existing hospitalisation,
4. results in persistent or significant disability or incapacity,
5. is a congenital anomaly/birth defect,
6. other important medical events which, in the opinion of the investigator, are likely to become serious if untreated, or as defined in the protocol

NOTES:

(i) The term “life-threatening” in the definition of “serious” refers to an event in which the patient was at risk of death at the time of the event; it does not refer to an event which hypothetically might have caused death if it were more severe.

(ii) Important medical events which may not be immediately life-threatening or result in death or hospitalization but which may jeopardize the patient or may require intervention to prevent one of the listed outcomes in the definition above should also be considered serious.

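### The grade 3-4 toxicity comparison has no valid window in the observation arm, compares laboratory and ECG events that are tested unequally, and is in tension with the SAE-only reporting sentence

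*Protocol*

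**What the plan says.** Secondary objective 2 (protocol section 6.2.2) is a between-arm comparison: "To compare the grade 3-4 toxicity between adjuvant metronomic chemotherapy and observation". Section 11.2 makes it operational: "To compare CTCAE version 4.03 worst grade toxicity between the 2 arms during any period of chemotherapy", by chi-square or Fisher's test. On timing, CTCAE "will be used to classify and grade the intensity of adverse events after each treatment cycle". The concept sheet repeats both statements. For the comparator, section 10.2 says "In arm A observation would be done".

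On testing, section 10.3.1 gives Arm B a visit schedule similar to that of Arm A, with one difference: "Except that ECG and LFT would be done at each visit". In Table 3 (Arm A), blood count, renal, liver and electrolyte tests at scheduled visits carry a footnote: "Investigations will be done as per institutional standards and sos".

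On recording, section 11.2 says "CTCAE will be used to collect all events regardless of attribution", while section 18 says "AEs are not required to be reported unless they meet SAE criteria".

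**The concern.** A between-arm comparison of worst grade needs the same observation window, the same detection effort and the same recording rule in both arms. The protocol fixes a window and a grading trigger that exist only in Arm B. It schedules more laboratory and ECG testing in Arm B, and it leaves unclear whether non-serious events reach the case record form.

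The protocol's argument for the regimen leans on low toxicity: the concept sheet calls it minimally toxic, and section 5 says there is no major grade 2-4 toxicity. The toxicity comparison is what would support or undermine that. Heavier testing in Arm B would overstate the difference between arms. Recording only serious events would understate toxicity. If both operate, the result cannot be read with confidence in either direction.

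**Working it through.** The protocol states no rate, power or sample size for toxicity, so there is no figure to reproduce. The main check sets the sections side by side.

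**1. Window.** Arm B's chemotherapy period is at most 18 cycles of 28 days (section 10.3.1): 18 × 28 = 504 days, or 504 / 30.4375 = 16.6 months. The concept sheet calls the treatment 18 months, about 548 days. Arm A has no chemotherapy and no cycles, and no section supplies an equivalent period, although its follow-up runs beyond year 5.

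To show that the choice matters, assume the same constant hazard in both arms and an incidence p over 504 days. The concept sheet puts grade 3-4 incidence below 5%, so p = 5% is its upper edge; 3% is also shown. Then h = −ln(1 − p) / 504, and incidence over w days is 1 − exp(−h·w).

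| Arm A window | p = 3% | p = 5% |
|---|---|---|
| 365 days | 2.2% | 3.6% |
| 504 days (as Arm B) | 3.0% | 5.0% |
| 548 days | 3.3% | 5.4% |
| 1,096 days | 6.4% | 10.6% |

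With no true difference, the Arm A rate falls below or above Arm B's according to the window an analyst picks.

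**2. Ascertainment up to 18 months.**

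| Item | Arm A (section 10.2, Table 3) | Arm B on treatment (section 10.3.1, Table 4) |
|---|---|---|
| Visits | 3-monthly | similar; Table 4 column says 3-monthly |
| Toxicity assessment | scheduled visits | scheduled visits |
| ECG | baseline only | each visit |
| Liver function | institutional standard or as needed; at progression | each visit |
| Electrolytes | institutional standard or as needed; at progression | scheduled |
| Blood count, renal function | listed without qualifier in year 1, as needed from year 2 (section 10.2); footnoted throughout in Table 3 | scheduled |

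At 3-monthly visits there are 18 / 3 = 6 occasions. The protocol itself fixes 6 liver tests and 6 ECGs in Arm B, and none of either in Arm A after baseline. For blood count and renal function it fixes 6 in Arm B against 12 / 3 = 4 in Arm A under section 10.2, or none under the Table 3 footnote. Those two places should be reconciled.

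The direction follows: a transient laboratory or ECG abnormality is more likely to be found in Arm B. The size needs a detection ratio that the protocol does not give. As an illustration only, assume 519 per arm (1,038 / 2, taking equal allocation), equal true rates, two-sided alpha 0.05, and a fraction d of Arm A events detected. With p1 the true rate, p2 = d·p1 and p̄ their mean, the chance of a significant false excess in Arm B is Φ[(p1 − p2 − 1.96·√(2p̄(1 − p̄)/519)) / √((p1(1 − p1) + p2(1 − p2))/519)].

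| True rate | d = 0.75 | d = 0.50 |
|---|---|---|
| 2% | 8.9% | 26.3% |
| 3% | 11.4% | 37.0% |
| 5% | 16.5% | 56.4% |

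The nominal chance in that direction is 2.5%. The table treats every counted event as dependent on these tests. For a total that also includes clinically evident toxicity, d would be nearer 1 and the effect smaller.

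**3. Recording.** Take a grade 3 laboratory abnormality that meets no SAE criterion. Under section 11.2 it is collected; under section 18 it need not be reported. Section 18 does not say whether reporting means entry on the case record form or expedited notification.

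**The case against.** The other side has good points.

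- Extra safety tests in a drug arm are normal and not an error in themselves. This stands: the problem is a formal between-arm test on events those tests detect.
- A reader might infer from the per-cycle grading and the 18 cycles that Arm B is assessed 18 times against 6 in Arm A. The documents do not support building on that. Section 10.3.1 makes the visit schedules similar, and the Table 4 column that mentions 18 cycles also says 3-monthly. The day-1 re-treatment criteria in section 10.3.4 point towards per-cycle checks, so the text is ambiguous, but the 3-monthly reading gives 6 against 6 and no difference in visit frequency.
- A reader might also infer that hepatic toxicity cannot be observed in Arm A. It can: Table 3 allows liver tests by institutional standard or as needed, and schedules them at progression. They are less certain, not absent. Likewise, section 10.2 lists year-1 blood counts and renal tests in Arm A without qualification.
- Collecting all events while reporting only serious ones is a coherent arrangement. Section 11.2 also says that the worst toxicity is recorded, and section 16 provides a case record form. This makes recording the weakest of the three parts: the section 18 sentence needs clarifying, and undercounting follows only on the adverse reading.
- The exact Arm A window could be left to a statistical analysis plan. That would hold if the protocol were silent. Here it states a rule that cannot apply to one arm, so an analysis plan would have to depart from it.
- This is a secondary outcome with no stated power, and the interim boundaries rest on survival. That limits the weight of the point.

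**Conclusion.** The point holds in three parts of differing strength.

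- **Window: firm.** The stated period and grading trigger do not exist in Arm A, so the rule gives no valid comparator.
- **Ascertainment: firm in direction.** ECG, liver function and electrolytes are tested unequally, as are blood count and renal function after year 1. A between-arm test on such events is biased towards an excess in Arm B. Clinically assessed toxicity is not affected in this way, because visits and toxicity assessment are scheduled in both arms. The size cannot be derived from the protocol; the percentages above rest on assumed rates, windows and detection fractions.
- **Recording: conditional.** Sections 11.2 and 18 are in unresolved tension. Non-serious grade 3-4 events are undercounted only if section 18 governs the case record form.

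The change should be made, but it does not touch the primary endpoint, the sample size or the survival boundaries.

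**What to change.** - In section 11.2 and the concept sheet, define one window for both arms, from randomisation to 18 months, with grading at the common 3-monthly visits. It covers 18 undelayed cycles even if treatment starts 30 days after registration (section 10.1), since 30 + 504 = 534 days against 548. Arm B events after 18 months, where cycles were delayed, can be described separately.
- Limit the chi-square or Fisher test to event types ascertained alike: clinically assessed toxicities, and blood count and renal findings only where both arms are tested on schedule. Reconcile section 10.2 with the Table 3 footnote so that this period is clear.
- Report ECG, liver, electrolyte and other unequally tested findings descriptively by arm, and state the testing difference.
- Reconcile section 18 with section 11.2: all CTCAE grade 3-5 events go on the case record form in both arms, and the SAE limit applies to expedited reporting only.

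The cost is amendment wording and a line on the case record form. No new test is needed in Arm A, and treatment is unchanged. The downside is that some laboratory toxicity is reported without a formal comparison. The recording rule should be settled early, because events never entered may not be recoverable at analysis.

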# 7 Hypothesis & trial design

Adjuvant metronomic chemotherapy will result in a 6.5% absolute improvement in 3-year OS rate, which would be considered a clinically meaningful increase .

This will be a 2 arm, parallel design, open label, superiority, explantory phase III randomized controlled trial with multiple interim analysis.

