## 13.2 Rationale for interim analysis

The survival benefit shown with adjuvant metronomic studies is limited sample size cohort studies. Hence as the investigators plan to do a study which is powered for an absolute survival improvement of 6% at 3 year in OS.It was decided to have a multiple interim analysis.

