## 13.3 Sample size justification

### 13.3.1 Sample size

The primary endpoint for is 3 year OS. The study assumes a 3 year OS in standard arm of 69%. With Type I error of 5% , Type II error of 20%, for a hazard ratio of 0.77, with study duration of recruitment of 9 years, study follow up of 3 years and 5 % lost to follow up the sample size was calculated using fixed design, two-arm trial with time-to-event

outcome (Lachin and Foulkes, 1986) in Rstudio version 3.2.1. The sample size required was 950 patients with analysis done at 485 events. However in view of the large sample size 3 interim analysis were included in this study using Group sequential design sample size with Hwang-Shih-DeCani spending function for time-to-event outcome events. The final **sample size was 1038 patients**. The analysis plan below shows events at each analysis with the decision rules.

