**Decision rules**

Upper bound spending computations assume trial continues if lower bound is crossed.

----Lower bounds---- ----Upper bounds-----

Analysis N Z Nominal p Spend+ Z Nominal p Spend++

1st interim 133 -0.75 0.2275 0.0203 2.95 0.0016 0.0016

2nd interim 265 0.13 0.5509 0.0335 2.58 0.0049 0.0044

3rd interim 398 0.91 0.8180 0.0552 2.17 0.0151 0.0118

Final analysis 530 1.69 0.9548 0.0910 1.69 0.0452 0.0322

Total 0.2000 0.0500

+ lower bound beta spending (under H1):

Hwang-Shih-DeCani spending function with gamma = -2.

++ alpha spending:

Hwang-Shih-DeCani spending function with gamma = -4.

Boundary crossing probabilities and expected sample size

assume any cross stops the trial

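### The FACT-H&N schedule does not supply the TOI scores that section 11.2 compares: by the table cells, Arm B has no forms after progression or at months 24 and 36, while Arm A can have them

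*Protocol*

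**What the plan says.** Section 11.2 has TOI calculated from FACT-H&N at baseline and at 6, 12, 18, 24 and 36 months in both arms and treats a rise of 6 units as significant. It then states: "Proportion of patients with significant improvement in TOI will be compared between 2 arms". A proportion test is named. The denominator, and how a patient who has died or has no form is counted, are not stated.

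Form collection is described in several other places:

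- Section 10.2 (Arm A) lists forms at baseline, 6, 12, 18 and 24 months. Its text for years three to five mentions none.
- Section 10.3.1 (Arm B) says visits resemble those of the observation arm, with ECG and LFT added. It does not mention the questionnaire.
- Table 3 (Arm A) ticks the form at baseline and at scheduled visits and crosses it out at progression.
- Table 4 (Arm B) ticks it at baseline, gives it a footnote mark in the chemotherapy column (up to 18 months), and crosses it out both after 18 months and at progression.
- The footnotes to both tables list 6, 12, 18, 24 and 36 months, counted from the start of chemotherapy, with no exception for progression.

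On survival, section 13.3.1 says "The study assumes a 3 year OS in standard arm of 69" per cent and sizes the trial "for a hazard ratio of 0.77".

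**The concern.** An analysis plan can settle how missing scores are treated. It cannot recover questionnaires that were never handed out. The places that govern collection disagree with section 11.2 and with each other, and they disagree differently for the two arms. If sites work from the table cells, as they commonly do, whether a patient has a late TOI score depends on the arm. Missing data that depend on the arm by design are the hardest kind to defend in an open-label comparison of patient-reported outcomes.

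A second issue follows. Under the trial's own hypothesis fewer patients die in Arm B, so the groups still able to complete a form differ in size by month 36. The late result then depends partly on whether the dead are left out or counted as not improved.

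**Working it through.** **1. Post-baseline forms by source**

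| Source | Arm | 6, 12, 18 months | 24 months | 36 months | After progression |
| --- | --- | --- | --- | --- | --- |
| Section 11.2 | both | yes | yes | yes | not addressed |
| Table footnotes | both | yes | yes | yes | no exception stated |
| Section 10.2 text | A | yes | yes | not listed | not addressed |
| Table 3 cells | A | yes | yes | yes | cross at progression; scheduled-visit column has no limit |
| Table 4 cells | B | yes, in chemotherapy column | cross | cross | cross at progression; chemotherapy column has ended |

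Section 10.4 ends study treatment at documented progression. An Arm B patient who progresses before month 18 therefore leaves the only column of Table 4 that schedules the form after baseline. The footnote attached to that column asks for months 24 and 36, which lie outside it. The footnote under Table 3 counts from the start of chemotherapy, which Arm A does not receive, so Arm A has no defined time origin.

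**2. The plan's own survival figures**

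The 485 events of the fixed design reproduce. With two-sided 5% and 80% power, events = 4 × (1.960 + 0.842)² / (ln HR)². For 69% vs 75%, HR = ln 0.75 / ln 0.69 = 0.7753 and the result is 485. This matches section 13.2, where the trial is "powered for an absolute survival improvement of 6% at 3 year in OS". The printed HR of 0.77 gives 460. For the present point the difference hardly matters. Three-year Arm B survival is 0.69^0.77 = 75.1% under HR 0.77, 75.0% under 6 points, and 75.5% under the "6.5% absolute improvement in 3-year OS rate" of section 7. Deaths by month 36 are thus 31.0% in Arm A against 24.9%, 25.0% or 24.5% in Arm B.

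**3. Deaths and patients able to give a form**

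Assumptions: 1:1 allocation of 1038 patients (519 per arm), constant hazard, HR 0.77, no loss to follow-up. Deaths by month m are 1 − 0.69^(m/36) in Arm A and 1 − 0.69^(0.77m/36) in Arm B. The number alive is 519 times the complement.

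| Month | Dead A | Dead B | Gap (points) | Alive A | Alive B |
| --- | --- | --- | --- | --- | --- |
| 6 | 6.0% | 4.7% | 1.3 | 488 | 495 |
| 12 | 11.6% | 9.1% | 2.5 | 459 | 472 |
| 18 | 16.9% | 13.3% | 3.6 | 431 | 450 |
| 24 | 21.9% | 17.3% | 4.6 | 405 | 429 |
| 36 | 31.0% | 24.9% | 6.1 | 358 | 390 |

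Under section 11.2 and the footnotes, up to 405 vs 429 forms are available at month 24 and 358 vs 390 at month 36. Under the table cells, the counts are up to 405 vs 0 and up to 358 vs 0. If section 10.2 governs Arm A, month 36 has none in either arm. The protocol gives no PFS rate, so the forms lost after progression cannot be counted.

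**4. How much the denominator matters at month 36 if all forms are collected**

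The protocol gives no TOI response rate; q = 30% to 50% is an assumption.

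- All randomised, death counted as not improved, survivors responding equally in both arms: the difference is q × (0.7515 − 0.690), or +1.8 points at q = 30%, +2.5 at 40% and +3.1 at 50%, in favour of Arm B. With 519 per arm this is 0.7 to 1.0 standard errors.
- Survivors only, no TOI effect in patients who would survive on either arm, and the extra Arm B survivors (390 − 358 = 32) responding at a fraction r of q: the Arm B rate is q × [0.690 + r × (0.7515 − 0.690)] / 0.7515.

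| r | Difference B − A (points) | Two-sided rejection at nominal 5% |
| --- | --- | --- |
| 1 | 0 | 5.0% |
| 0.5 | −1.2 to −2.0 | 6.6% to 8.6% |
| 0 | −2.5 to −4.1 | 11.5% to 20.1% |

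**The case against.** The best defence is that the tables can be read to agree with section 11.2. The progression column describes the visit at which progression is found: biopsy is ticked only there. A cross in it need not stop later calendar forms. The footnotes list all five visits without exception, section 10.3.1 aligns Arm B visits with Arm A, and section 10.4 says follow-up continues after treatment stops. This reading is fair for the progression column. It does not remove the explicit cross for Arm B after 18 months, and it does not supply month 36 in section 10.2. The follow-up sentence in section 10.4 refers back to this same protocol, and it is written for patients who stop study treatment, so it does not plainly cover an observation arm.

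A second defence is that rules for death and missing forms in a secondary quality-of-life outcome are commonly left to the SAP, which is not shown. That stands: their absence here is not in itself an error.

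A reader might go further and infer that the proportion test necessarily compares unequally selected survivors and is biased against an effective Arm B. The documents do not support that. Section 11.2 speaks only of a proportion of patients; an all-randomised denominator fits the words equally well and tilts the result the other way. The gap in deaths belongs to the alternative hypothesis. With equal survival it disappears, and at month 6 it is only 1.3 points.

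**Conclusion.** The collection schedule contradicts the outcome it has to serve. Followed by the cells, Table 4 leaves Arm B without forms at months 24 and 36, where about 429 and 390 patients should be alive under the plan's alternative, and without forms after progression. Table 3 allows both in Arm A, while section 10.2 omits month 36. The late TOI comparison is then impossible, or it is made between differently selected patients. This conclusion rests on the text of the tables and needs no modelling; the patient counts assume 1:1 allocation, constant hazard and HR 0.77.

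The denominator is a lesser issue. The choice moves the month-36 difference by a few points in either direction, from −4.1 to +3.1 over the assumed response rates. Its size and sign rest on those assumptions, so no single bias figure can be claimed. The choice is one of estimand and may properly sit in the SAP. TOI is a secondary outcome; the primary survival analysis is not affected.

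**What to change.** Reconcile section 10.2, Tables 3 and 4 and their footnotes with section 11.2:

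- FACT-H&N at 6, 12, 18, 24 and 36 months in both arms, with the Table 4 cell after 18 months corrected and month 36 added to section 10.2.
- One time origin that exists in both arms, such as randomisation.
- A statement that the calendar forms continue after progression for patients who are alive and in follow-up, whatever the progression-visit cell shows.

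Before the data are seen, in section 11.2 or the SAP, state the TOI denominator and how death counts. Report both the all-randomised and the survivors-only result, and name which one leads. Neither is neutral: counting death as not improved carries survival into the TOI result, while restricting to survivors compares groups formed after randomisation.

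The cost is a few corrected table cells, a footnote and a sentence or two, plus one questionnaire at visits already made for follow-up. Forms missed while the schedule remains unclear cannot be recovered later.

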| Outcome Measures | 1. 3 year OS : OS will be defined time in days between date of randomization to date of death. Patients alive at their last follow ups would be censored. The OS would be estimated by Kaplan meier analysis and would be compared between the 2 arms by the log rank test. Cox proportional hazard model would be constructed for calculation of hazard ratio. 2. 3 year PFS : PFS will be defined time in days between date of randomization to date of progression or death whichever is earlier. Patients who have not progressed or died at their last follow ups would be censored.The median PFS would be estimated by Kaplan meier analysis and would be compared between the 2 arms by the log rank test. Cox proportional hazard model would be constructed for calculation of hazard ratio. 3. Toxicity : To compare CTCAE version 4.03 worst grade toxicity between the 2 arms during any period of chemotherapy. Chi- square test or fisher's test would be used for comparison. The NCI Common Terminology Criteria for Adverse Events version 4 (NCI CTCAE v4.03) will be used to classify and grade the intensity of adverse events after each treatment cycle. 4. TOI ( Trial outcome index) : TOI will be calculated at baseline and at 6, 12,18,24,36 months in both arms from FACT Head and neck QOL proformas. Increment in TOI of 6 units would be considered significant. The proportion of patients showing an increment in TOI between the 2 arms would be compared by Proportion test. |
| Feasibility | Each year we treat 600 patients with CTRT. Hence if post CTRT each year even if we can recruit 120 patients than in 9 years the recruitment would be over. Hence this study is feasible. |
| Significance | Head and neck cancers are one of the most commonest cancers in the country. Most present locally advanced state. The current options produce unsatisfactory outcomes. Addition of oral metronomic chemotherapy in multiple retrospective studies has been associated with improvement in survival. Hence this study is planning to test this hypothesis. If successful this will be a cost effective and minimally toxic treatment option for patients. |
| Funding | Both intramural and extramural funding options will be explored |
| Risks | Oral metronomic therapy in the study conducted by Pai et al had no grade 3-4 side effects. Even in international studies the incidence of grade 3-4 side effects is below 5%. Hence this seems to be a safe option |

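### The only TOI analysis counts patients who improve by 6 units, which does not answer the objective of comparing QOL scores, treats worsening as no change, and makes no adjustment for baseline.

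*Protocol*

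**What the plan says.** The secondary objective (Protocol 6.2.2, repeated in substance in the concept sheet) is: "To compare the 6,12,18,24 & 36 months QOL scores between the 2 arms".

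Section 11.2 sets the measurement times: "TOI will be calculated at baseline and at 6, 12,18,24 & 36months in both arms from FACT Head and neck QOL proformas". It then sets a threshold, "Increment in TOI of 6 units would be considered significant", and the analysis: "Proportion of patients with significant improvement in TOI will be compared between 2 arms. Proportion test would be used for comparison". The concept sheet names the same test: "The proportion of patients showing an increment in TOI between the 2 arms would be compared by Proportion test".

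No other analysis of TOI is named. The threshold covers gains only, and there is no matching category for a loss. No comparison of means, use of the repeated measurements or adjustment for baseline TOI is mentioned.

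**The concern.** The objective speaks of scores and the analysis delivers a count of improvers. A reader of the final report could not obtain the promised difference in scores from the stated method.

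The direction also matters. Arm B takes two oral drugs for up to 18 cycles and Arm A is observed, so a natural QOL question is whether treatment makes patients feel worse. Under section 11.2, a loss of 20 units and no change at all are the same result. A harm confined to patients who would not have gained 6 units anyway leaves the test statistic unchanged.

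Splitting a score at one cut also discards precision. A finding of no difference would then say less about QOL than the collected data allow.

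**Working it through.** The protocol states no power, SD, responder rate or correlation for TOI, so there is no figure of its own to reproduce. All inputs on the score itself are assumptions and are shown as ranges.

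**1. Objective against analysis.** Section 6.2.2 asks for a comparison of scores at five times. Section 11.2 and the concept sheet compare the proportion gaining 6 units. These are different quantities.

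**2. Information kept against mean change.** For a normally distributed change and a small shift, the relative efficiency of a split with proportion p improving is φ(z)²/[p(1−p)], where z is the normal quantile for p.

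- p = 0.25: 0.3178²/0.1875 = 0.54
- p = 0.35: 0.3704²/0.2275 = 0.60
- p = 0.50: 0.3989²/0.25 = 0.64, the best case

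**3. Information kept against a baseline-adjusted mean.** With correlation ρ between baseline and follow-up and equal SDs, the adjusted variance divided by the variance of change is (1−ρ²)/[2(1−ρ)] = (1+ρ)/2. This is 0.70 at ρ = 0.4 and 0.80 at ρ = 0.6.

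- Lower end: 0.54 × 0.70 = 0.38
- Upper end: 0.64 × 0.80 = 0.51

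**4. What this means for power.** Section 13.3.1 states that the "sample size was 1038 patients". The allocation ratio is not stated; 1:1 is assumed, giving 1038/2 = 519 per arm. The same section says "The study assumes a 3 year OS in standard arm of 69" per cent, and 519 × 0.69 = 358. To allow for some missing forms, 340 per arm is taken as a late-visit size. Further assumptions are an SD of change of 15, ρ = 0.5, a true shift of 3 units and a two-sided 5% test.

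| Patients per arm | Proportion improving | Mean change | Baseline-adjusted mean |
|---|---|---|---|
| 519 | 71% | 90% | 96% |
| 340 | 53% | 74% | 85% |

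Over SDs of 12-18, shifts of 2-3 units and both sizes, the proportion test has 21-88% power and the adjusted mean 39-99.6%.

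**5. Worsening, general.** Take a mean change of zero under observation and a downward shift in Arm B, with 340 per arm. At SD 15, a 6-unit fall takes the proportion improving from 34.5% to 21.2%, and the planned test detects it with 97% power (91-99.7% for SD 18 down to 12). For a 3-unit fall, power is 51% (39-68% over the same SDs).

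**6. Worsening, confined to non-improvers.** Suppose 30% improve in both arms but 15% v 30% worsen. The planned test then rejects only at its 5% error rate, while a test of worsening with 340 per arm has 99.7% power. This example is built to show the blind spot and is not a forecast.

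**7. Collection at later visits.** Section 11.2 and the footnotes to Tables 3 and 4 require QOL at 24 and 36 months. The body of Table 4 marks QOL as not done after 18 months in Arm B. Section 10.2 lists forms up to 24 months and none at 36. These places conflict.

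**The case against.** A pre-specified responder threshold on a secondary endpoint is a legitimate choice, and covariates, repeated-measures structure and handling of missing forms commonly sit in an SAP, which is not shown here. That is fair as far as it goes. But the protocol itself fixes the variable, the threshold and the test, and that test does not answer its own objective.

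Three stronger readings are tempting, and the document does not support them.

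- **That the analysis ignores baseline.** TOI is measured at baseline, and an increment most naturally means change from it. Only adjustment for baseline is missing, which under randomisation costs precision and does not bias.
- **That the plan inflates false positives.** Each single test holds about 5% (4.4-5.6% in simulation). Only if any one of five unadjusted 5% tests could support a claim would the chance of a false one reach 1 − 0.95⁵ = 22.6% if independent, or about 20% when simulated with correlated visits. The protocol states no such claim rule and does not say in words that the test is repeated at each visit. The "With Type I error of 5% , Type II error of 20%, for a hazard ratio of 0.77" statement concerns overall survival only.
- **That the rule is blind to harm.** Step 5 shows that it would usually detect a general fall of 6 units. What it loses is power for small shifts and any view of worsening outside the improver group.

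It is also true that a mixed model does not resolve deaths: later visits still describe survivors. A ceiling in TOI would limit means as well as counts, and the protocol gives no baseline distribution from which to judge it.

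**Conclusion.** The concern holds in this form: the stated TOI analysis is dichotomised, looks at improvement only, is not adjusted for baseline, and does not match the objective of comparing scores. The mismatch and the missing category for worsening follow from the text alone and need no assumption.

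The loss of precision does rest on assumptions. With 25-50% improving and normal changes, 36-46% of the information is lost against mean change. With ρ of 0.4-0.6 as well, 49-62% is lost against a baseline-adjusted mean. A flat statement that half the information is lost would go beyond the document, because the figure depends on the responder rate, the correlation and the comparator.

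This is a secondary endpoint, so the primary survival conclusion is untouched. The correction is worth making because it is cheap and concerns the patient-reported cost of the treatment.

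**What to change.** In section 11.2 and the concept sheet:

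1. Make the main TOI analysis a baseline-adjusted comparison of mean TOI between arms, for example a repeated-measures model with baseline TOI, arm, visit, arm-by-visit interaction and the stratification factors (site, T stage, N stage).
2. Name one headline visit, report the mean difference there with its 95% CI, and treat the other visits as descriptive.
3. Keep the 6-unit threshold as a supportive summary, giving the proportions that improve and that worsen by at least 6 units from baseline.
4. State that later visits describe patients who are alive and assessed.
5. Reconcile the QOL collection rules in section 10.2, in the body and footnote of Table 4, and in section 11.2, so that both arms follow one schedule.

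The cost is a few sentences, the commitment to one headline visit, and slightly more analysis work. No data are needed beyond those section 11.2 already calls for, provided that item 5 settles whether the 24- and 36-month forms are collected in both arms.
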